**Classification of protocol violation**

Not applicable

- 1. PRIMARY DATA ANALYSES

**Primary Outcomes**

*Sufficient response rates for representativity of subgroups*

As expected, study participation will vary depending on gender, age, diagnosis, and healthcare utilization, but this can be compensated for by weighting the study participants according to structural information on the target population.

Within our study, data on the above-mentioned patient characteristics is available for both participants and the whole target population. Weighted measures from participants will be compared with measures of the complete target and will be assumed to be formally representative if the weighted measures from participants fall within the 95% confidence interval of the same measures based on data of the complete target population.

The general methodology (see 5.1) will be applied for the analysis of the primary outcomes.

**Secondary Outcomes**

Value of care:

Value of care delivery is assessed according to the Porter value-based healthcare framework:

Patient-Value = Outcome/Costs

In the analysis, we will firstly focus on the outcome side of the value equation and assess the outcome side based on PROMs and PREMs. The categorization into suspected high-value and suspected low-value care is hence based on PROMs and PREMs. Outcomes higher than average in at least two survey periods are classified as suspected high-value care whereas outcomes lower than average in at least two survey periods are classified as suspected low-value care. Outcomes not included in one of the categories will be separated and excluded from analysis (see Figure 4).

[figure not shown]

*Figure 4: Assessment of Value-Based Healthcare - Outcome dimension*

|  | **PROM – outcome (health)** | **PREM – outcome (responsiveness)** |
| --- | --- | --- |
| **Suspected low-value care** | Maximum one standard deviations above average in at least two survey periods | Maximum one standard deviations above average in at least two survey periods |
| **Suspected high-value care** | Maximum one standard deviations below average in at least two survey periods | Maximum one standard deviations below average in at least two survey periods |
| **Measure-ment** | Separately for health-related quality of life (PROPr index score) & disease-specific health (index score of the disease-specific PROM):   - COPD-related health status - Asthma-related health status - Coronary artery disease-related health status - Diabetes-related health status (for both types) | German responsiveness questionnaire index score |

*Table 1: Assessment of Value-Based Healthcare - Outcome dimensions and measurement*

To cover the cost-side of the value equation as well, we add the health care system utilization. For each of the chronic diseases average treatment costs will be calculated. Costs will cover all healthcare related costs (see 2.6 secondary data). Depending on the deviation from the average participants are classified in the following categories:

- Low costs: More than one standard deviation below average in at least two survey periods
- High costs: More than one standard deviation above average in at least two survey periods
- Inconspicuous costs: Else

Based on the combination of PROMs, PREMs and health care system utilization measured as costs, a value-based healthcare cube is introduced. PROM and PREM scores function as outcome dimensions and healthcare system utilization as cost dimension. Costs are hence added as new axis inside the framework (see Figure 5).

[figure not shown]

*Figure 5: Assessment of Value-Based Healthcare - Framework*

The newly introduced value-based healthcare cube allows the measurement of high-value and low-value care. Along the previously defined areas of suspected high- and low-value care (see Figure 4 and 5), the cube can be subdivided into 27 segments (see Figure 6). High-value and low-value care will be investigated based on the following criteria:

- High-value indication in both dimensions (high patient-relevant indicators (PROMs/PREMs) **at** low costs) (Figure 6 – dark green area)
- High-value indication in at least one dimension (high patient-relevant indicators (PROMs/PREMs) **or** low costs) (Figure 6 – light green area)
- Low-value indication in at least one dimension (low patient-relevant indicators (PROMs/PREMs) **or** high costs) (Figure 6 – light red area)
- Low-value indication in both dimensions (low patient-relevant indicators (PROMs/PREMs) **at** high costs) (Figure 6 – dark red area)

The value of care dimensions will be summarized into high- versus low-value care as the broad definition and into high two-sided, high one-sided, low one-sided and low two-sided value care as narrow definition. For both categorizations the frequency as well as the variation per subgroups (e.g. region, DMP etc.) will be analyzed.

[figure not shown]

*Figure 6: Assessment of Value-Based Healthcare – Framework distinguishing between high- and low-value care*

*Outcome and experience variation*

Mean change in PROM and PREM-index (sub-)scores overall and per subgroup (see 5.1 and 4.3) per disease area over time:

- Average per survey period
- Consistency over time (test-retest reliability)

Meaningful change / Minimally clinical important difference (MCID) in PROM index (sub-)scores overall and per subgroup (see 5.1 and 4.3) per disease area over time:

- Average per survey period
- Consistency over time (test-retest reliability)

*Hospital admission risk based on PROMs/PREMs and patient characteristics*

- Using machine learning predictive models (long-short-term memory deep learning network for time trend classification, random forest, logistic regression, decision tree and/or support vector machine) to identify admission risk in Q3 and Q4 based on PROMs/PREMs in Q1 and Q2

*PRO feedback*

- Mainly: Statistically significant change in at least one of the health care behavior dimensions (see 4.2) and comparison of participants who opened the report vs. those who did not, using logistic regression (change/no change)
  - Physical activity: Shift of participants to a higher category
  - Nutrition: Shift of participants to “More healthy” from any other category
  - Tobacco: Shift of participants to a lower category
  - Alcohol: Shift of participants to a lower category
  - Sleep: Share of stable participants (no significant variation in sleep duration)
- Secondly: Descriptive exploratory analysis of the rates of the following two evaluation dimensions and statistically significant differences in subgroups (see 5.1 and 4.3):
  - Understandability
  - Helpfulness
  - Emotional change

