An initial invitation letter is sent to 200,000 insured individuals, 50,000 of each of the selected chronic conditions (about 25,000 per sub-cohort). Diabetes type 1 and type 2 are considered jointly as there is no differentiation in the selected PROMs. The patients of all chronic diseases are allocated to groups based on their participation in DMP (DMP or non-DMP group). Prior experiences suggest that around 30% of patients react to invitations to participate in research by their insurer [29-31]. Two-thirds of initial participants are expected to allow follow-up contacts and around 40% of these patients will continue participating in all the follow-up surveys after receiving reminders for each task. Therefore, after accounting for non-participants and participants with no complete survey data we expect a complete data set for 16,000 participants. However, the first research question will investigate response rates as there is no evidence on this population yet.

- 1. STUDY PROCEDURE

Eligible participants will be participating in the study for a maximum of four quarters, starting with the first access of the digital questionnaires followed by quarterly digital surveys split into several tasks. To start the survey, participants register with their study pseudonyms and share personal information, e.g., basic demographics and identification data. Each survey period contains four tasks to be completed by participants defined as sets of questions that each will take five to ten minutes to complete. The participants are invited to answer PROM and PREM surveys.
[figure not shown]

*Figure 1: Study design: Participants’ timeline and tasks*

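### Value-of-care labels rest on the level of PROM scores and total costs with no allowance for severity or comorbidity within a disease, so the labels and their shares partly reflect case mix

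*Protocol*

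**What the plan says.** Section 1.2 asks how far variation in the value of care can be identified, and what share of care is low- or high-value per indication and in subgroups. Section 5.2 (Secondary Outcomes, Value of care) sets the rule:

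- **Basis of the outcome axis.** "The categorization into suspected high-value and suspected low-value care is hence based on PROMs and PREMs".
- **Direction in the prose.** "Outcomes higher than average in at least two survey periods are classified as suspected high-value care", while "outcomes lower than average in at least two survey periods are classified as suspected low-value care".
- **Table 1 differs.** Its low-value row reads "Maximum one standard deviations above average in at least two survey periods", which reverses the direction and brings in a standard-deviation band that the prose does not have.
- **Cost axis.** "For each of the chronic diseases average treatment costs will be calculated". The scope is wide: "Costs will cover all healthcare related costs (see 2.6 secondary data"). High and low cost mean more than one SD from that average in two or more periods.
- **Cube.** Poor indicators or high costs give a one-sided low-value label. Both together form the two-sided cell: "Low-value indication in both dimensions".

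On diabetes, section 2.5 states: "Diabetes type 1 and type 2 are considered jointly as there is no differentiation in the selected PROMs".

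**The concern.** In chronic disease, a health score and total healthcare spending plausibly depend on disease stage and comorbidity as well as on care. Greater severity would tend to lower the PROM score and raise cost, so both axes push the same patients towards the two-sided low-value cell. A patient with advanced, multimorbid disease may be well treated and still score below the average and cost more than it.

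The share of each label, overall and by region or DMP status, is the reported answer to secondary objective 1. If the labels carry severity, part of that share and part of any subgroup difference describes who is ill rather than who is well cared for.

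Diabetes is a special case on the cost axis. Type 1 patients need an insulin prescription to enter (section 2.3). If the four disease areas of section 2.1 define the cost averages, they are judged against a joint type 1/type 2 average. The reason given for pooling concerns the PROMs and does not extend to cost.

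**Working it through.** **1. The plan's own figure.** The protocol gives no expected share of low-value care and no severity effect. Its one derived number, the complete data sets in section 2.5, reproduces (200,000 × 0.30 × 2/3 × 0.40 = 16,000) but is not an input here.

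**2. Does anything in the rule allow for severity?**

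| Element | Where | Changes the label? |
|---|---|---|
| Disease-specific PROMs and cost averages | 5.2 | Allows for which disease, not how severe |
| Peer groups by disease, gender, age | 2.4 | No; used for the feedback report |
| DMP/non-DMP matching on diagnosis; strata of age, gender, utilization | 2.5 | No; shapes the invited sample |
| Subgroup analyses, including utilization | 5.1 | No; follow the labels |
| Regressions on significant patient characteristics | 5.2, Data analysis | No; severity is not named |
| Mean change and MCID | 5.2 | No; separate outcomes |

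No element puts severity, comorbidity or an expected score into the classification.

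**3. Size on one score axis (assumptions, not protocol figures).** For 1,000,000 simulated patients and four periods:

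score in period t = −√s·Severity + √c·Care + √(r/2)·Person + √(r/2)·Noise(t), with r = 1 − s − c

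All terms are independent standard normal, so the score has mean 0 and SD 1; higher means better health. Low-value means below the cut in at least 2 of 4 periods. The cut is 0 for the prose rule and −1 for a possible SD-based rule. Care share c = 10%.

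| Severity share s | Prose rule: sickest vs mildest quartile | 1-SD cut: sickest vs mildest quartile |
|---|---|---|
| 10% | 76% vs 40% | 31% vs 7% |
| 50% | 93% vs 14% | 51% vs 0.4% |

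At s = 30% the 1-SD cut gives 42% vs 2%. As a control, a separate simulation (within-person correlation 0.7) with no severity effect gives about 58% low-value in both the sickest and the least-sick tenth under the prose rule.

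**4. Effect on a subgroup comparison.** For two groups with identical care, one 0.3 SD sicker, at s = 50% and the 1-SD cut, the low-value share is 20.5% vs 14.7%, a gap of 20.5 − 14.7 = 5.8 percentage points with no difference in care.

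**5. What adjustment achieves** (s = 50%, c = 10%, 1-SD cut). The proportion of all low-value labels falling in the sickest quartile is:

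- unadjusted: 72%
- adjusted with a severity measure of reliability 0.5: 49%
- adjusted with severity measured perfectly: 25%, the value expected if severity plays no part

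The cost axis, the PREM axis and the combined cube cells were not simulated.

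**The case against.** A reader might infer that the sickest patients are labelled low-value whatever care they receive. That is not supported. At s = 50%, c = 10% and the 1-SD cut, 100 − 51 = 49% of the sickest quartile escape the label, and 70% of all those labelled had worse-than-median care. Nor does mild disease with poor care reliably end in a high-value cell: for the mildest quartile with worst-fifth care the proportion is about 25% under the 1-SD cut and about 82% under the plain-average rule.

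Other points in the plan's favour:

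- **Matching, stratification and regression.** These bear on the DMP, regional and age comparisons, so it cannot be said that such differences would simply be case mix. But matching applies to invitees, of whom about 30% are expected to respond. None of these steps alters a label or an overall share.
- **The PREM** measures responsiveness, and nothing in the protocol ties it to severity. This stands, and the point is limited accordingly.
- **Reference group.** The group behind the PROM and PREM averages is not defined in the text, and Figure 4 is not available here. Age- or sex-specific averages are not excluded, but they would still leave severity within a disease unaddressed.
- **Assumptions.** The variance shares have no source in the protocol. With c = 30% (s = 50%, 1-SD cut), labels going to better-than-median care fall from 30% to 17%.
- **Diabetes.** A joint cost average is plausible from sections 2.1 and 2.5 but not stated outright, and its effect is not quantified.
- **Wording.** The outcome-axis labels are called suspected. The cube, however, is presented as measuring high- and low-value care without that qualifier.

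**Conclusion.** The point holds in limited form. The rule in section 5.2 classifies value of care from score level and all-healthcare cost level, with no term for severity or comorbidity within a disease. The labels and their shares therefore partly reflect case mix, mainly through the PROM and cost axes. Later regressions may reduce confounding in comparisons but leave the shares as they are.

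The illustrated size is 76–93% of the sickest quartile against 40–14% of the mildest under the prose rule, and 31–51% against 7–0.4% under a 1-SD cut. It rests on normal scores, higher meaning healthier, a care share of 10% and a severity share of 10–50%. It shows direction and possible scale; it is not an estimate for this study. All of it follows the direction given in the prose, which Table 1 contradicts.

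This should be fixed. It is not critical to the trial: value of care is a secondary outcome, and the primary endpoint of representativeness is unaffected.

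**What to change.** 1. Reconcile the prose in section 5.2 with Table 1: one direction per instrument, one cut-off, and a stated reference group for each average.
2. In section 5.2, classify on observed minus expected PROM score and cost. Model the expected values within each disease from pre-invitation claims (age, sex, comorbid diagnoses, earlier utilization), leaving out DMP status and region, whose variation is to be studied. Apply the agreed cut-offs to the standardised residuals.
3. Handle type 1 and type 2 diabetes separately, at least on the cost axis.
4. Keep the unadjusted classification as a sensitivity analysis, presented as health-status and cost groups rather than as value of care.
5. State two limits: adjustment removes case mix only as far as claims measure severity, and severity markers that result from earlier care are adjusted away.

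The cost is revised wording and one regression per score and per cost measure in each disease. The data types are already in the claims list of section 2.6, provided the extract covers the period before invitation; no new survey items are needed. The labels become somewhat harder to explain.

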**Patient reported indicators:**

- Generic PROM index score: PROMIS PROPr is a preference-based score which combines seven PROMIS domains of health status into one score (cognitive function, depression, fatigue, pain, physical function, sleep, social roles)
- Disease-specific PROM index scores for each chronic disease

Asthma: Asthma Impairment and Risk Questionnaire (AIRQ) score

COPD: Clinical COPD Questionnaire (CCQ) score

Diabetes: Problem Areas in Diabetes (PAID-5) score

Coronary artery disease: Seattle Angina Questionnaire (SAQ-7) score and Rose Dyspnea Scale (RDS) score

- PREM index score: Responsiveness of the health care system
- Looked at PRO feedback
- Comprehensibility of PRO feedback
- Helpfulness of PRO feedback
- Emotional reaction to PRO feedback
- Discussion of PRO feedback with physician(s)
- Health behavior in five dimensions:

Physical activity

Nutrition

Tobacco consumption

Alcohol consumption

Sleep duration

- Plans to change health behavior in the future
- Trigger for health behavioral change
- Overall health improvement
- Disease-specific health improvement

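### The value-of-care rule applies one direction to every PROM index score, the text and Table 1 disagree on which direction, and no scoring direction or recoding is stated

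*Protocol*

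**What the plan says.** Section 5.2 (Secondary Outcomes, Value of care) sets the rule in running text: "Outcomes higher than average in at least two survey periods are classified as suspected high-value care". The rule for the opposite class mirrors it: "outcomes lower than average in at least two survey periods are classified as suspected low-value care". The description of the value cube later in that section keeps this direction: "High-value indication in both dimensions (high patient-relevant indicators (PROMs/PREMs" and so on.

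Table 1, under the same heading, assigns the directions the other way round. Its row for suspected low-value care reads "Maximum one standard deviations above average in at least two survey periods", and its row for suspected high-value care reads "Maximum one standard deviations below average in at least two survey periods". The wording is the same in the PROM and PREM columns.

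The measurement row says which PROM scores are classified: "Separately for health-related quality of life (PROPr index score) & disease-specific health (index score of the disease-specific PROM", followed by the four diseases. Section 2.6 names the instruments. PROPr is described there as a preference-based score combining seven health domains. The disease-specific list has AIRQ for asthma, CCQ for COPD, "Diabetes: Problem Areas in Diabetes (PAID-5) score" and "Coronary artery disease: Seattle Angina Questionnaire (SAQ-7) score and Rose Dyspnea Scale (RDS) score". The protocol does not give the scoring direction of any of these, and it mentions no reversal or recoding.

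**The concern.** A single direction is safe only if all classified scores run the same way. The names suggest that they may not: PROPr is presented as a measure of health, while AIRQ, PAID-5 and RDS are named for impairment and risk, problems and breathlessness. If the set is mixed, reconciling the text with Table 1 in either direction still leaves some scores mislabelled. The orientation problem therefore needs its own fix, beyond removing the contradiction.

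The shares of suspected high- and low-value care, per indication and by subgroup, are a stated secondary objective (section 1.2) and secondary outcome (section 4.2). On a mis-oriented score, the patients doing best would be counted as suspected low-value care, and comparisons such as DMP versus non-DMP on that score would point the wrong way. The same patients' PROPr labels could meanwhile be right.

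Coronary artery disease has a further gap that needs no scoring assumption. Section 2.6 lists two scores, while Table 1 speaks of one index score of the disease-specific PROM, so it is unclear which score carries the label.

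**Working it through.** **1. Directions side by side**

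| Place in section 5.2 | Suspected high-value | Suspected low-value |
| --- | --- | --- |
| Running text | above average | below average |
| Value cube | high PROM/PREM | low PROM/PREM |
| Table 1 | below average (up to 1 SD) | above average (up to 1 SD) |

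Each version has one direction for all scores. Suppose PROPr rises with better health and at least one disease score rises with worse health (both are assumptions). The text then suits PROPr and fails on that disease score; Table 1's direction suits that disease score and fails on PROPr. No single direction suits both.

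**2. What the text rule does to an unrecoded higher = worse score**

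Let *h* be health and *s* = −*h* the score. Then *s* is above its average exactly when *h* is below its average. With four periods and no ties, let *a* be the number of periods in which *h* is above average:

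- *a* = 3 or 4: high-value only on *h*, low-value only on *s*.
- *a* = 0 or 1: low-value only on *h*, high-value only on *s*.
- *a* = 2: meets both definitions on *h* and on *s*, so nothing changes.

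The swap is complete among patients with one label and absent among those who meet both definitions.

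**3. How many carry only one label**

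The protocol gives no within-patient correlation, so the ICC is an assumption. With normally distributed scores over four periods, simulation gives:

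| Assumed ICC | Meet both definitions | One label only (1 − both) |
| --- | --- | --- |
| 0.3 | 26.0% | 74.0% |
| 0.5 | 20.1% | 79.9% |
| 0.7 | 14.4% | 85.6% |
| 0.9 | 7.8% | 92.2% |

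As a plausibility check, at ICC = 0 the share meeting both would be C(4,2)/2⁴ = 6/16 = 37.5%. The simulated shares fall from there as the ICC rises, as they should.

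In the healthiest tenth of patients, the text rule labels 99.4% to 100% as high-value only when the score is oriented higher = better. When the same score is left higher = worse, it labels 99.4% to 100% as low-value only and none as high-value only.

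**4. How many patients are exposed**

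Section 2.5 gives 200,000 invited, about 30% reacting, two-thirds allowing follow-up and around 40% of these completing all surveys:

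200,000 × 0.30 × 2/3 × 0.40 = 16,000,

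which reproduces the protocol's figure. With four diseases invited in equal numbers and equal response assumed, 16,000 / 4 = 4,000 complete data sets per disease. Swapped labels per affected disease would then be 4,000 × 0.74 = 2,960 to 4,000 × 0.92 = 3,680, plus partial responders with at least two periods.

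**The case against.** The strongest counter-argument is that a raw-score reading is not compelled. The text speaks of outcomes rather than scores, and Table 1 heads its PROM column as health and lists disease-related health status; a higher health outcome is naturally better health. The patient report in section 2.4 says whether scores are better or worse than the peer group's, so the sponsor must already know each instrument's direction. Aligning questionnaire scores is also a derivation step often left to an analysis plan, and that plan is not shown.

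This makes an actual reversal less certain, but it does not repair the rule. Table 1 names index scores as what is measured, and the better/worse wording of the patient report is not carried into section 5.2. For health behavior, the same section sets directions item by item (a higher category for activity, a lower one for tobacco and alcohol). The point is also not that detail is missing: the protocol states a direction, states it uniformly, and states it in two opposite ways.

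It is also fair to object that names are weak evidence of scoring. SAQ-7 is named for a complaint, PROPr includes depression, fatigue and pain, and the name CCQ says nothing about direction. That stands, and it is why the consequence is conditional.

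A reader might infer more than the protocol supports:

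- **That higher = high value is the plan's one rule.** Table 1 says the opposite.
- **That every label on an affected score is inverted.** Patients who meet both definitions do not change.
- **That whole invited cohorts of 50,000 are affected.** Non-responders are never labelled.
- **That the value cube is reversed for the disease.** Its PREM and cost axes do not depend on how a disease PROM is oriented, and PROPr is classified separately.
- **That CCQ must be reversed.** Nothing in the protocol shows which way it runs.

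**Conclusion.** The point holds in a conditional form. Two facts need no assumption: the text and Table 1 give opposite directions, and each applies its direction uniformly to PROPr and all disease-specific indices without an orientation step. That the coronary label has two candidate scores is equally plain.

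The mislabelling rests on an assumption the protocol neither confirms nor excludes, namely that at least one of AIRQ, PAID-5 and RDS is scored higher = worse and is analyzed unrecoded. In that case the text rule swaps the labels on that score for about 74% to 92% of patients with four periods (assumed ICC 0.3 to 0.9), or roughly 3,000 to 3,700 of about 4,000 expected complete data sets per affected disease. Under Table 1's direction the error falls on PROPr instead.

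Only the disease-specific PROM axis of a secondary outcome is touched under the text rule. The primary endpoint and the sample-size figures are not affected, and the error can be corrected at analysis. It is still worth correcting, because the rule as written cannot be right for scores that run in different directions.

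**What to change.** In section 5.2, before the classification rule, add that every PROM and PREM index is oriented so that higher means better, and list the scoring direction or the recoding for each: PROPr, AIRQ, CCQ, PAID-5, SAQ-7, RDS and the responsiveness index. Then define suspected high-value care as better than average, and suspected low-value care as worse than average, on the oriented score. Use that wording in the text, in Table 1 and for the cube. The same edit should settle whether Table 1's one-standard-deviation limit, which the text does not mention, belongs to the rule.

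For coronary artery disease, state whether SAQ-7 and RDS are classified separately or which of them carries the label.

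The cost is a sentence and a table row. Data collection and sample size do not change.

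### Section 5.2 defines suspected high- and low-value care twice: Table 1 runs against the text in direction and cut-off, and neither rule gives the three exclusive levels that the cube needs

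*Protocol*

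**What the plan says.** All of this stands in Protocol section 5.2, under Secondary Outcomes, Value of care.

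- **Text rule.** The high-value side reads "Outcomes higher than average in at least two survey periods are classified as suspected high-value care". The low-value side of the same sentence mirrors it: "outcomes lower than average in at least two survey periods are classified as suspected low-value care". No standard-deviation threshold is given. The next sentence adds: "Outcomes not included in one of the categories will be separated and excluded from analysis".
- **Table 1.** The row for suspected low-value care reads "Maximum one standard deviations above average in at least two survey periods". The row for suspected high-value care reads "Maximum one standard deviations below average in at least two survey periods". Each wording appears in both the PROM and the PREM column. It therefore covers the generic index, every disease-specific index and the responsiveness score.
- **Cost axis.** "Low costs: More than one standard deviation below average in at least two survey periods". High costs mirror this, and everyone else is inconspicuous.
- **Cube.** Outcomes and costs are combined and "the cube can be subdivided into 27 segments". The criteria that follow treat high PROMs and PREMs as high value and low ones as low value.

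Section 2.1 sets four quarterly survey periods. Section 4.2 lists the shares of low- and high-value care as outcomes for the second research question and refers to the statistical section for their definition.

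**The concern.** The protocol itself fixes the rule, so a later analysis plan has no neutral starting point: whichever version it adopts contradicts the other. Four faults can be read off the page.

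1. **Direction.** Table 1 ties above-average scores to low value. The text and the cube tie them to high value.
2. **Cut-off.** The text uses any deviation from the average, Table 1 at most one SD, and the cost axis more than one SD.
3. **Overlap.** With four periods and a two-period requirement, a patient above average twice and below average twice meets both text definitions. No precedence is stated.
4. **Missing middle.** The text rule leaves nobody unclassified when four periods are complete, ties aside. Yet the protocol sets aside an unclassified group and builds a cube with three levels per axis.

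At stake are the reported shares of high- and low-value care and their comparison by region, DMP status and other subgroups. Two programmers working faithfully from this section could report different, and in part opposite, classifications.

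**Working it through.** **Side by side**

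| Source | High value | Low value | Distance from average |
|---|---|---|---|
| Text | above average | below average | any |
| Table 1 | below average | above average | at most 1 SD |
| Cube criteria | high PROM/PREM | low PROM/PREM | not stated |
| Cost axis | low cost | high cost | more than 1 SD |

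Every row except the cube criteria also requires at least two periods. The cube and the text agree on direction, and Table 1 stands alone. Scales on which a higher score is worse cannot reconcile them. The protocol states no scoring direction, and the same Table 1 wording covers all instruments. If all were scored that way, the text and the cube would be wrong instead.

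**Levels needed.** 27 = 3 × 3 × 3, so PROM, PREM and cost each need three levels.

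**Inputs for the size.** Four periods come from section 2.1. The rules are those above. Standard normal scores with equal correlation ρ between periods are an assumption, since the protocol gives neither. The range is ρ = 0.5 to 0.85, with 1,000,000 simulated patients per value. The protocol states no figure for these shares, so there is none to reproduce.

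**Exact checks of the text rule.** A patient is in both categories when exactly two of four scores are above average.
- ρ = 0: C(4,2)/2⁴ = 6/16 = 37.5%.
- ρ = 0.5: the number of above-average periods is uniform on 0 to 4. Hence P(2) = 1/5 = 20% and P(at least 2) = 3/5 = 60%.
- Nobody is in neither category: four non-tied scores cannot have fewer than two above and fewer than two below. High + low − both = 60 + 60 − 20 = 100%.

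**Two readings of Table 1**
- *Bands*: low = mean < score ≤ mean + 1 SD; high = mean − 1 SD ≤ score < mean; each in at least two periods.
- *Cut-offs*: low = score ≤ mean + 1 SD; high = score ≥ mean − 1 SD; each in at least two periods.

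**Simulated shares of all patients (%)**

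| Rule | ρ | High | Low | Both | Neither |
|---|---|---|---|---|---|
| Text | 0.5 | 60 | 60 | 20 | 0 |
| Text | 0.85 | 55 | 55 | 10 | 0 |
| Table 1, bands | 0.5 | 43 | 43 | 9 | 23 |
| Table 1, bands | 0.85 | 42 | 42 | 9 | 25 |
| Table 1, cut-offs | 0.5 | 93 | 93 | 86 | 0 |
| Table 1, cut-offs | 0.85 | 88 | 88 | 76 | 0 |
| Cost rule applied to outcomes | 0.5 | 17 | 17 | about 0 | 66 |
| Cost rule applied to outcomes | 0.85 | 18 | 18 | about 0 | 65 |

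**What the band reading does to good scorers.** Of patients who are high-value only by the text, about 73% become low-value only and none becomes high-value. Of patients more than 1 SD above average in at least two periods, 63-70% are unclassified and 30-34% are labelled low-value.

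Only the cost rule gives a middle level with practically no overlap.

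**The case against.** **Intent is recoverable.** The sentence before Table 1 and the cube criteria give the direction, and the cost bullets below it show a workable rule with a residual level. The likely history is two swapped rows plus poor wording. This stands as a reason for a lower severity. It does not remove the contradiction: swapping the rows alone still leaves the wrong distance rule.

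**A reader might infer that coding from Table 1 simply reverses the answer.** That holds only under the band reading. Under the cut-off reading the rows overlap almost entirely, and the fault is double classification.

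**A reader might infer that excluding the middle group forces the low-value share to 50% whatever the care.** The documents do not support this, because it needs symmetric scores, which are nowhere stated. With mildly left-skewed scores (−exp(0.5z), the same correlations, a rule of more than 1 SD) the low share among the classified was about 57-59%. Nor are subgroup shares forced to 50%. Any cut-off set relative to the cohort's own mean and SD ties the overall share to the shape of the distribution, and the fix below does not change that.

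**A reader might infer that the cube's own categories overlap.** By wording alone, "High-value indication in at least one dimension" and its low-value counterpart can both be true of one cell. If PROM or PREM alone suffices, the count is 27 − 8 − 8 + 1 = 12 of 27 cells; if both are needed, it is 2 of 27. But each criterion is tied to a coloured area of Figure 6, which is not available here and may allocate every cell. This remains a question to check.

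**The exclusion sentence** belongs to the outcome-only step and points to Figure 4, also not available. It does not say that the middle group leaves the cube, and 27 segments suggest that it stays. The text rule nevertheless cannot produce that group from four complete periods.

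**Conclusion.** The point holds in this form: section 5.2 is wrong as written, because the text and Table 1 conflict in direction and cut-off, and neither yields the three-level outcome axis that the cube requires. The contradiction rests on the wording alone. Its size depends on assumed normal scores, four complete periods and a correlation of 0.5 to 0.85:

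- Table 1 as bands leaves about 63-70% of clearly high scorers unclassified.
- Table 1 as cut-offs double-classifies about 76-86% of patients.
- The text rule double-classifies about 10-20%.

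The overlap under the text rule comes from having four periods. With exactly three completed, a patient cannot meet both definitions, and there is still no middle level.

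Severity is should-fix. The affected shares are secondary, descriptive outcomes of the second research question. The primary endpoint on representativeness does not use them, and no sample-size figure depends on them.

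**What to change.** 1. State the scoring direction of each index and orient all of them so that higher is better before classification.
2. Swap the two rows of Table 1.
3. Use one rule in both text and table, the one that the protocol already applies to costs. High is more than 1 SD above the disease-specific average in at least two survey periods, low is more than 1 SD below it in at least two, and everyone else is inconspicuous.
4. Assign the rare patient who meets both definitions to inconspicuous. In the simulation this was about 0.01% of patients or fewer at correlations of 0.5 and above, and 0.4% at zero correlation.
5. Replace the exclusion sentence: keep the inconspicuous group in the denominator of the reported shares and in the cube.
6. Check Figure 6. If it does not already allocate cells with one favourable and one unfavourable dimension, state which category receives them.

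The cost is a corrected table, a few sentences and a consistency check of Figures 4 to 6. No new data are needed and the surveys do not change.
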